**6.9. Color Assessment**

Color evaluation will be performed on the upper incisors and canines of each volunteer with an EasyshadeAdvanced spectrophotometer (Vita-Zahnfabrik, Germany), using the CIE L*a*b* system, where the values ​​of color change (E) were obtained for each group of teeth using the formula: E = {(L)2 + (a)2 + (b)2}1/2 , where: L* = L*- L*0; a* = a*-a*0; and b* = b*- b*0. The color evaluation will be performed at three times: before the whitening treatment serving as a baseline, 21 days and 1 month after the last application of the whitening gel.

## **6.10. Sensitivity assessment**

## Postoperative sensitivity will be evaluated through a daily questionnaire that will be provided to volunteers from the first at-home bleaching treatment session, which must be completed during the 21 days of treatment, according to their personal perception and pain threshold, on the level of sensitivity or discomfort caused by the bleaching treatment, on a scale from 0 (no pain) to 10 (severe pain), according to Visual Analogue Scale.

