**RESEARCH PROJECT**

**5 – OBJECTIVE**

This randomized, placebo-controlled clinical trial aims to evaluate the effect of 1.5% potassium oxalate in controlling pain sensitivity and color change after at-home tooth whitening. The null hypotheses tested in the present study will be: H01 - There will be no difference in tooth sensitivity between the groups bleached with 22% carbamide peroxide associated or not with 1.5% potassium oxalate, thirty days after the end of treatments.

H02- There will be no difference in color change between the groups bleached with 22% carbamide peroxide associated or not with 15% potassium oxalate, thirty days after the end of treatments.

H03- Use of 1.5% potassium oxalate after bleaching treatment will not influence Health-Related Quality of Life (HRQoL).

H04- Use of potassium oxalate after bleaching treatment will not influence patient satisfaction.

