**G2 (n=25)**

Experimental Group

(1.5% Potassium Oxalate)

Pain assessment by daily questionnaire

(n=50)

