**6.6 Intervention**

Each volunteer in the group will receive a kit containing a tube with Polanight bleaching agent (SDI, SP, Brazil), two individual trays of ethylene/vinyl acetate copolymer (upper and lower), an unmarked tube with the desensitizer (potassium oxalate at 1.5%), a toothbrush and a fluoride-free toothpaste (My First Colgate®, Colgate-Palmolive Company, SP, Brazil).

*-Dental whitening*

The volunteers will be molded with alginate (Jeltrate Plus - Dentsply) with the aid of a tray (Tecnodent). Then, the models will be made using special plaster (Durone-Dentsply). The trays will be made from the models obtained using an ethylene/vinyl acetate copolymer (FGM) plate and a vacuum plasticizer (Plastivac P7/Bio Art). It will be recommended to apply a drop of the whitening agent Polanight (SDI, SP, Brazil) on each corresponding tooth in the tray that should be used for 45 minutes a day for a period of twenty one days.

- *Placebo*

After the bleaching treatment, the trays will be washed with running water, and the volunteers in group 1 will apply a small amount of the placebo gel, without active ingredient, with a color, texture and odor similar to 1.5% oxalate gel (Painless, BM4, SC, Brazil) in the spaces related to the buccal portions of the teeth of the trays, which should be used for 10 minutes. After removing the tray, the patient should brush the teeth with the fluoride-free toothpaste (My First Colgate®, Colgate-Palmolive Company, SP, Brazil).

*- Treatment with 1.5% Potassium Oxalate*

After the bleaching treatment, the trays will be washed with running water, and the volunteers in group 1 will apply a small amount of 1.5% oxalate gel (Painless, BM4, SC, Brazil) in the spaces related to the buccal portions of the teeth of the teeth trays, which should be used for 10 minutes. After removing the tray, the patient should brush their teeth with fluoride-free toothpaste (My First Colgate®) and clean the tray in order to remove all the gel inside the tray.

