## **6.11. Assessment of Oral Impact on Daily Performance (OIDP)**

## The OIDP will be used to measure the oral impact caused by bleaching treatment on individuals' ability to perform daily activities. It includes nine performances to be evaluated, based on the model by Masalu (2003),42 which analyzes physical, psychological and social activities, including eating, speaking and pronouncing correctly; teeth cleaning; sleep and relax; smiling, laughing and showing teeth without feeling ashamed and maintaining the emotional state without getting angry. For each reported impact, the patient will record the main symptom (1- tooth sensitivity, 2- tooth color, or 0- other reason). This questionnaire will be provided before and after the whitening treatment.

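### The daily score in section 6.10 covers more than H01 does: it is not limited to the teeth, and a single combined score cannot be split afterwards

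*Protocol*

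**What the plan says.** Section 5 of the protocol states H01 in terms of the teeth: "There will be no difference in tooth sensitivity between the groups bleached with 22% carbamide peroxide", with or without potassium oxalate. The aim in the same section uses a looser term: "evaluate the effect of 1.5% potassium oxalate in controlling pain sensitivity and color change after at-home tooth whitening".

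Section 6.10 gives the measure. It opens with "Postoperative sensitivity will be evaluated through a daily questionnaire". Volunteers fill this in themselves on each of the 21 treatment days, and the score is described as being "on the level of sensitivity or discomfort caused by the bleaching treatment, on a scale from 0 (no pain) to 10 (severe pain"). No site is recorded and no second item is described. Figure 1 labels the same instrument "Pain assessment by daily questionnaire".

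Section 6.11 (OIDP) handles causes differently. For each impact on daily life, "the patient will record the main symptom (1- tooth sensitivity, 2- tooth color, or 0- other reason"). That questionnaire is given only before and after whitening.

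Under section 6.6, bleaching gel is worn in an upper and a lower tray for "45 minutes a day for a period of twenty one days" in both arms, and each session is followed by the study gel in the same trays.

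**The concern.** The hypothesis names one sensation, and the measure accepts either of two. As described, discomfort felt outside the teeth but put down to the bleaching is a legitimate answer. The mechanisms given for oxalate in sections 3 and 4 of the protocol, tubule blocking and an effect on nerve endings, concern the teeth. Discomfort arising elsewhere would therefore probably carry little information about the question in H01.

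What is at stake is how the result can be read. If part of the score has nothing to do with the teeth, a null result is harder to interpret as no effect on tooth sensitivity. This is not something a later analysis plan can repair: once a volunteer has written one combined number, nothing else in the protocol allows it to be separated. The OIDP cannot do it, because it is not a daily record and it asks about impacts on activities.

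**Working it through.** **Wording side by side**

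| Place in the protocol | What is named |
|---|---|
| Section 5, H01 | tooth sensitivity |
| Section 5, aim | pain sensitivity |
| Section 6.10, opening | postoperative sensitivity |
| Section 6.10, item | sensitivity or else discomfort, attributed to bleaching, with pain anchors |
| Figure 1 | pain |
| Section 6.11, OIDP | tooth sensitivity kept apart from tooth color and other reasons |

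Only H01 and the OIDP name the teeth. The pain anchors do not restrict the site, and neither does the attribution to bleaching.

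**What a broader score could cost**

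The protocol gives no power, effect size or standard deviation, so there is no figure of its own to reproduce. From the document: 25 per arm (Figure 1) and a 5% significance level (section 6.13). Two-sided testing is assumed, and so is every other input below.

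*Model A: the other discomfort adds to the score, equally in both arms.* Take as reference the standardised difference that gives 80% power:

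d = (1.960 + 0.842) × √(2/25) = 2.802 × 0.2828 = 0.792.

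If the added variance is r times the variance of tooth sensitivity, the mean difference is unchanged and the SD grows by √(1 + r). Power is then Φ(d/√(1 + r) × √(25/2) − 1.960).

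| r | d/√(1 + r) | Power |
|---|---|---|
| 0 | 0.792 | 80% |
| 0.10 | 0.756 | 76% |
| 0.25 | 0.709 | 71% |
| 0.50 | 0.647 | 63% |
| 1.00 | 0.560 | 51% |

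For r = 0.50: 0.647 × 3.536 − 1.960 = 0.33, and Φ(0.33) = 0.63.

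*Model B: the volunteer reports the worse of two sensations.* Simulated trials of 25 v 25 used tooth scores with mean 3.6 (placebo) and 2.0 (oxalate), SD 2, clipped to 0–10, compared by a rank-sum test. A share of volunteers in both arms also has other discomfort. Results move by about a point of power between simulation runs.

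| Other discomfort (assumed) | Share affected | Difference between arms | Power |
|---|---|---|---|
| none | 0% | 1.46 | 76% |
| mean 1, SD 1 | 20% to 50% | 1.43 to 1.36 | 75% to 74% |
| mean 3, SD 1.5, on 5 of 21 days, diary averaged | 20% to 50% | 1.44 to 1.37 | 77% to 75% |
| mean 3, SD 1.5, one score per volunteer | 20% | 1.33 | 68% |
| same | 30% | 1.25 | 63% |
| same | 50% | 1.11 | 56% |

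The last three rows are severe: the assumed discomfort (mean 3) exceeds the assumed tooth score in the oxalate arm (mean 2.0), and its presence throughout the diary is implied.

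In Model A only precision suffers. In Model B the difference itself shrinks as well. With no discomfort outside the teeth, both models lose nothing.

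**The case against.** The strongest reply is that section 6.10, read whole, already means tooth sensitivity. Its heading and opening words say sensitivity, the anchors are pain, and the introduction names only tooth sensitivity as a common unwanted effect of home bleaching. On that reading, discomfort is just a lay synonym. The diary form itself is not in the document either, so its exact wording to volunteers is unknown. This reply has force: it means that contamination is possible, not shown. It does not close the gap, because volunteers answer alone and by their own perception, and the description offers discomfort as an alternative to sensitivity.

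A reader might go further and infer any of the following. The document does not support them.

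- *Gum or tray discomfort does enter the score.* The protocol mentions neither, so whether they occur is unknown.
- *Any oxalate effect is diluted.* Additive noise that is equal in both arms leaves the mean difference where it was. The difference shrinks only under something like the worse-of-two model.
- *A volunteer with discomfort elsewhere is counted as sensitive.* No sensitive/not-sensitive rule exists; section 6.13 analyses the reported values.
- *The primary outcome is defined in two ways.* No outcome is named primary. H01 comes first, and sensitivity is the only outcome that section 6.13 names, but that is not a designation.
- *One gel soothes or irritates the gums and so biases the comparison.* Nothing in the protocol bears on this.

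The OIDP comparison is also limited. It shows that the protocol treats tooth sensitivity as one cause among several, but it does not show that the diary is wrong.

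**Conclusion.** The point holds as a mismatch of scope. The item described in section 6.10 is broader than H01, it permits discomfort outside the teeth to be scored, and the combined score cannot be separated later. The consequence is conditional on such discomfort occurring. The illustrations run from practically no loss (76% to about 75%) to a large one (80% to 51%, or 76% to 56%). They rest wholly on assumed means, SDs and shares, and nothing in the document selects among them. They show direction and possible range and are not an estimate for this trial. This is a cheap improvement worth making rather than a demonstrated defect in the result.

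A separate issue lies in the same sections: H01 is set "thirty days after the end of treatments", while the diary covers only the 21 treatment days. Rewording the item does not resolve that.

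**What to change.** In section 6.10, and on the diary form, word the daily item as tooth sensitivity, meaning pain felt in the teeth, scored 0 to 10. Add a separate line on the same diary page for any other discomfort. State that the sensitivity hypothesis is tested on the tooth item only and that the other line is reported descriptively by arm. If the form already asks about the teeth alone, it is enough to bring the description in section 6.10 into line with it.

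The cost is one reworded item and one extra line per day for 21 days, so a slightly longer diary. No extra visits, staff or volunteers are needed.

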## **6.11. Assessment of Oral Impact on Daily Performance (OIDP)**

## The OIDP will be used to measure the oral impact caused by bleaching treatment on individuals' ability to perform daily activities. It includes nine performances to be evaluated, based on the model by Masalu (2003),42 which analyzes physical, psychological and social activities, including eating, speaking and pronouncing correctly; teeth cleaning; sleep and relax; smiling, laughing and showing teeth without feeling ashamed and maintaining the emotional state without getting angry. For each reported impact, the patient will record the main symptom (1- tooth sensitivity, 2- tooth color, or 0- other reason). This questionnaire will be provided before and after the whitening treatment.

## **6.12. Assessment of the degree of patient satisfaction with the bleaching treatment**

## At the end of treatment, patients will be asked to express themselves using a 7-point scale, based on the modified model by Kothari et al. (2020),43 the degree of satisfaction with the treatment. The scale will be graded from 1 (not at all satisfied) to 7 (very satisfied). Participants will also use the scale to express whether they would recommend the whitening protocol to their family and friends, choosing from 1 (would not recommend) to 7 (would recommend). Volunteers will also answer a questionnaire with five questions about their satisfaction with the whitening protocol used and the results achieved with the treatment. For each question, the volunteers will indicate one of the following scores: 1- I totally agree; 2 - I partially agree; 3 - no opinion; 4 - I somewhat disagree and 5 - I totally disagree.

## **6.13. Statistical analysis**

## The sensitivity values ​​reported by the volunteers will be tabulated in an Excel spreadsheet (Microsoft Windows 2010) and analyzed using the BioEstat.® program. If this study generates non-parametric data, the Friedman test will be performed for intragroup analysis and the Wilcoxon test for intergroup analysis. For all analyses, significance levels of 5% will be considered.

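### The protocol fixes 5% for every analysis of a 21-day sensitivity diary but no single between-arm test of H01, whose only stated time point lies outside the diary

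*Protocol*

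**What the plan says.** - **Hypothesis (section 5).** H01 is a between-arm null hypothesis: "There will be no difference in tooth sensitivity between the groups bleached with 22% carbamide peroxide associated or not with 1.5% potassium oxalate". It is tied to one time point, "thirty days after the end of treatments". H02 to H04 follow on colour, quality of life and satisfaction. The four are not ranked.
- **Measurement (section 6.10).** "Postoperative sensitivity will be evaluated through a daily questionnaire", scored 0 to 10, "which must be completed during the 21 days of treatment". No sensitivity score is scheduled after day 21. By contrast, section 6.9 does schedule a colour reading one month after the last gel application.
- **Analysis (section 6.13).** If the data turn out non-parametric, "the Friedman test will be performed for intragroup analysis and the Wilcoxon test for intergroup analysis". Then: "For all analyses, significance levels of 5% will be considered". The section does not say which day, or which summary of the 21 scores, enters the between-group test, or how many such tests are run.

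**The concern.** Each participant contributes 21 scores, and H01 needs one answer. The protocol fixes the error rate per analysis but not what is analysed. The one anchor it gives for H01, the 30-day time point, cannot be used because no sensitivity score is taken then. Someone therefore has to choose a day, a set of days or a summary, and nothing in the protocol stops that choice from being made after the results are seen. A claim that oxalate reduces sensitivity could then rest on one or two days that differ by chance.

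A second route to a wrong claim is the within-arm test. Change over days can be significant in one arm and not in the other when the arms do not differ. Such a contrast does not test H01.

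**Working it through.** **Inputs from the protocol.** 5% per analysis (6.13); 21 daily scores on a 0 to 10 scale (6.10); 25 participants per arm (Figure 1). The protocol states no family-wise error rate, so there is no figure of its own to reproduce.

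**Assumptions.** Tests are two-sided. The between-group Wilcoxon test is read as the rank-sum test for independent arms. Day-to-day correlation is not given, so a range is shown.

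**Step 1: upper reference.** If all 21 days are tested and the days are independent, the chance of at least one false-positive day is 1 − 0.95^21 = 0.659, or 66%.

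**Step 2: correlated days.** Scores from one person are correlated, which lowers this figure. With no true difference, 200,000 sets of 21 correlated two-sided z statistics gave the following chance of at least one day below 0.05:

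| Correlation | Equal for all pairs of days | Falling with the gap between days (AR(1)) |
|---|---|---|
| 0.3 | 55% | 64% |
| 0.5 | 43% | 60% |
| 0.7 | 30% | 52% |
| 0.9 | 16% | 32% |
| 0.95 | 12% | 22% |
| 0.99 | 8% | 11% |

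**Step 3: the rank test on diary-like scores.** Scores were simulated as normal values (mean 1, standard deviation 2.5), rounded down to whole numbers and limited to 0 to 10, with 25 per arm and 1,500 runs per setting. The tie-corrected rank-sum test on each of 21 days gave:

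| Correlation before rounding | Equal | AR(1) |
|---|---|---|
| 0.3 | 59% | 65% |
| 0.5 | 48% | 61% |
| 0.7 | 36% | 54% |
| 0.9 | 21% | 38% |

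These are mostly a little above step 2, as expected, because rounding and the floor at 0 weaken the correlation between days.

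**Step 4: size.** For correlations from 0.9 down to 0, the risk is 16% to 66%, or 16/5 ≈ 3 to 66/5 ≈ 13 times the nominal 5%. At 0.99 it is 8% to 11%, roughly twice nominal.

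**Step 5: one test instead.** In the same simulated diaries, a single rank-sum test on each participant's 21-day mean rejected in 3.9% to 5.9% of runs. The simulation standard error is √(0.05 × 0.95 / 1,500) = 0.6 percentage points, so this is consistent with 5%. Keeping all 21 tests would need 0.05/21 = 0.0024 per day under Bonferroni.

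**The case against.** **Does the protocol prescribe 21 daily tests?** A reader might infer this, since Friedman needs repeated scores and a daily between-arm comparison is its obvious counterpart. The text does not say so. One between-group test on a mean, a peak or a weekly score fits section 6.13 equally well, and then the error stays at 5%. This objection stands: the inflation is allowed by the wording, not fixed by it. Both named tests also apply only if the data are non-parametric.

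**Is this matter for a statistical analysis plan?** A plan that is not shown might name a summary, and the handling of missed diary days belongs there. Figures for participants lost to Friedman through missed days would rest on assumed missingness and are not part of this point. What remains is what the protocol itself states: 5% for all analyses, and an H01 time point that its own measurement schedule does not serve.

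**Is Friedman offered as the test of H01?** No. It is labelled intragroup and stands beside a separate intergroup test. It misleads only if one-arm significance is read as a treatment effect.

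**Is 66% the realistic figure?** No. It needs independent days, which is implausible within one person. It also counts days favouring either arm; days favouring oxalate alone would give 1 − 0.975^21 = 41% under independence.

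**Do four hypotheses at 5% add a further 18.5%?** That is 1 − 0.95^4, which again assumes independence. The hypotheses concern four different outcomes, and adjusting across them is debatable. Ranking them is enough.

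**Conclusion.** The point holds in a conditional form. The protocol does not give one well-defined 5% test of H01: the diary yields 21 scores, no between-arm summary or primary outcome is named, every analysis is set at 5%, and H01's only time point has no sensitivity data. This much rests on the text alone.

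The size depends on conduct. If all 21 days were compared unadjusted, the false-positive risk would be about 16% to 66% for correlations from 0.9 down to 0, and less above 0.9. If one pre-named summary or day were tested, it would be about 5%. It would go too far to say that the plan fixes 21 comparisons, or that it uses the within-arm test to decide H01. The weakness is worth correcting because the remedy is simple and restores the nominal error rate.

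**What to change.** In section 6.13:

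1. Make H01 the single primary hypothesis. Test it once, at two-sided 5%, by a rank-sum (Mann-Whitney) test on each participant's mean of the available daily scores over days 1 to 21, with a stated minimum number of days.
2. Report daily scores and the within-arm Friedman results descriptively, and say that neither is evidence of a difference between arms.
3. Label H02 to H04 secondary.

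In the same edit, reconcile H01's time point in section 5 with the diary window in section 6.10. A diary mean cannot serve as the test of H01 while H01 still refers to 30 days after treatment. Make the change before outcomes are compared by arm.

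**Cost.** Rewording of sections 5 and 6.13; no new data if H01 is aligned with the diary. Single-day differences can no longer be claimed as confirmatory, and a 21-day mean dilutes an effect confined to a few days. The daily curves would still show such a pattern descriptively.

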**RESEARCH PROJECT**

**7 – GOALS**

**-** The bibliographic survey will take place from August 2020 to December 2021;

- After approval by the Bioethics Committee, a randomized clinical trial will begin: the recruitment, randomization and allocation of volunteers, treatment, sensitivity assessment and color change will take place from August 2020 to September 2021.

- Tabulation and statistical analysis of the results will be carried out in the period between October and December 2021;

- The preparation and delivery of the final report will take place until December 2021

**7 – SCHEDULE OF ACTIVITIES**

| ACTIVITIES | ANO: 2020 / 2021  MONTHS | | | | | | | | | | | | | | | |  |
| --- | --- | --- | --- | --- | --- | --- | --- | --- | --- | --- | --- | --- | --- | --- | --- | --- | --- |
| A | S | O | N | D | J | F | M | A | M | J | J | A | S | O | N | D |
| Bibliographic survey | X | X | X | X | X | X | X | X | X | X | X | X | X | X | X | X | X |
| Submission to the bioethics committee |  |  |  | X | X |  |  |  |  |  |  |  |  |  |  |  |  |
| Volunteer screening | X | X | X |  |  |  |  |  |  |  |  |  |  |  |  |  |  |
| Conducting the clinical trial | X | X | X | X | X | X | X | X | X | X | X | X | X | X |  |  |  |
| Tabulation of results and statistical analysis |  |  |  |  |  |  |  |  |  |  |  |  |  |  | X | X | X |
| Delivery of the final report of the research project |  |  |  |  |  |  |  |  |  |  |  |  |  |  |  |  | X |
